Complications linked to hepato-intestinal schistosomiasis are increasing in the area of Richard-Toll, Northern Senegal. These cases are being identified at the local health centre. However, considering the high prevalence of schistosomiasis in this region, it is likely that the number of severe cases is much higher. Clear guidelines for the management of such severe complications and criteria for referral and surgery are required in this region. The establishment of an algorithm on how to treat these patients and create the appropriate infrastructure is urgently needed. The priority is how to take care of these patients and more so what is the best way of doing this under local conditions. One of the first steps is to critically evaluate the Niamey-Belo-Horizonte ultrasound methodology in patients with severe periportal fibrosis. Efficient management of bleeding varices in the afflicted patients is imperative.

Given the background that somatostatin is an ideal vasoactive drug in the field of liver pathology, it is our opinion that somatostatin will be more efficacious and safe as compared to currently used beta blocker drugs like propanolol, in the control of acute oesophageal variceal bleeding due to *Schistosoma mansoni *infection. Moreover using this neuropeptide may increase time to failure of drug treatment, decrease incidences of early re-bleeding (day 4, 8) and incidences of death during the follow up period. Decreased frequencies of late rebleeding (days 30, 60, 90) may occur, all indicating the safety of using somatostatin. Praziquantel cover would be given to all study patients.

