#### 4. Control points

A two part questionnaire will be set up to control treatment outcomes. The pre-treatment part of the clinical questionnaire will identify inclusion criteria questions:

(1) When was the last haematemesis incidence?

(2) When did the present incident start?

The post-treatment part of the questionnaire will identify treatment outcomes. The following questions will be answered:

(1) What was the reaction to somatostatin infusion?

(2) When did bleeding stop after somatostatin infusion?

(3) GI disturbances: Is there abdominal pain, nausea, diarrhea, after somatostatin infusion?

(4) Control of early rebleeding: Is there early rebleeding in the 8 days following somatostatin administration?

(5) Control of late rebleeding: When is the next rebleeding incident? Subjects will be followed up on a monthly basis, by home visits.

(6) Control of mortality: Is there any difference in mortality time between the two groups.

(7) Control of fibrosis: Does ultrasonography detect anti-fibrotic effect of somatostatin after treatment?

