## Discussion

It is expected that the administration of somatostatin as a bolus followed by a 24 hour long infusion, will stop bleeding immediately, delay rebleeding as compared to the control study group and delay mortality in the somatostatin treated subjects. Our protocol that is based on a pilot study will help to establish the importance of somatostatin in schistosomiasis.

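### Post-treatment questions 1 to 4 are anchored to somatostatin, so as printed they give control patients no time zero and no applicable question

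*Protocol article*

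**What the plan says.** The only outcome instrument that the protocol article describes is the two-part questionnaire under *4. Control points*. Its post-treatment part has seven items.

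- Item 1: "What was the reaction to somatostatin infusion".
- Item 2: "When did bleeding stop after somatostatin infusion".
- Item 3, on gastrointestinal disturbances: "Is there abdominal pain, nausea, diarrhea, after somatostatin infusion".
- Item 4, on early rebleeding: "Is there early rebleeding in the 8 days following somatostatin administration".
- Item 5, on late rebleeding: "When is the next rebleeding incident? Subjects will be followed up on a monthly basis, by home visits".
- Item 6, on mortality: "Is there any difference in mortality time between the two groups".
- Item 7 asks whether ultrasonography shows an anti-fibrotic effect of somatostatin.

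Under *2. Treatment*, the somatostatin group receives a bolus and a 24-hour infusion. The control group receives propranolol and praziquantel; no infusion and no start time are described for it.

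The expectations are comparative. The Background states that "it is our opinion that somatostatin will be more efficacious and safe as compared to currently used beta blocker drugs like propanolol", and goes on to anticipate fewer early rebleeds at days 4 and 8. The Discussion expects somatostatin to "delay rebleeding as compared to the control study group".

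**The concern.** A between-arm comparison needs the same question, asked over the same period and counted from the same kind of event, in both arms. Items 1 to 4 are fixed to an event that happens in one arm only. Site staff with a control patient in front of them must either leave these items blank or choose a substitute clock. In the first case the control side of the comparison is missing. In the second, the period covered and the thoroughness of questioning can differ by arm, which biases the comparison in a direction that cannot be predicted.

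The outcomes exposed are tolerability, the time bleeding stopped and rebleeding within 8 days. Tolerability matters most, because items 1 and 3 are the only printed questions on adverse effects and the Background makes a comparative statement about safety. The Background also presents less frequent rebleeding as a sign of safety. Rebleeding is an efficacy outcome and cannot stand in for adverse-effect data from both arms.

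**Working it through.** The protocol gives no figure on this point, so the check sets each item against the control arm as described.

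| Item | Outcome | Anchor as printed | Usable for a control patient as worded? |
|---|---|---|---|
| 1 | Reaction | Somatostatin infusion | No |
| 2 | Time bleeding stopped | Somatostatin infusion | No |
| 3 | Gastrointestinal disturbances | Somatostatin infusion | No |
| 4 | Rebleeding within 8 days | Somatostatin administration | No |
| 5 | Next rebleeding | No drug named | Yes |
| 6 | Mortality time | Both groups named | Yes, as a study-level question |
| 7 | Fibrosis on ultrasonography | Effect of somatostatin | Only if reworded and both arms are scanned |

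Four of seven items are anchored to somatostatin dosing, one more (item 7) names somatostatin alone, and two apply to both arms: 4 + 1 + 2 = 7.

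Next, the expectations against the items that would support them:

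- **Safety relative to propranolol (Background).** Supported only by items 1 and 3, both worded for one arm.
- **Less early rebleeding, days 4 and 8 (Background).** Supported directly by item 4, worded for one arm. Item 5 may help indirectly.
- **Delayed rebleeding relative to control (Discussion).** Supported by item 5 in both arms.
- **Delayed mortality (Discussion).** Supported by item 6 in both arms.
- **Immediate stopping of bleeding (Discussion).** Supported by item 2, worded for one arm. The reference to the control group in that sentence attaches to rebleeding, so a between-arm comparison of time to haemostasis is not explicitly announced there.

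Finally, does another section supply a common clock? The primary variable under *3. Data analysis* is counted over the infusion period, so it does not. Randomisation happens in both arms, but the questionnaire does not refer to it.

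An illustration of why the clock matters: the infusion lasts 24 hours, and the wording of items 1 to 4 does not say whether time runs from its start or its end. Suppose, as an assumption, that staff count 8 days from the end of infusion in one arm and from the start of treatment in the other. The windows are then displaced by 24 hours out of 8 × 24 = 192 hours, or 24/192 = 12.5% of the window, and the displaced part is the first day.

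**The case against.** The strongest reply is that the list is shorthand and not the form itself. Item 6 cannot be put to any patient; it is a question for the study to answer. The questionnaire is still to be set up, and a journal article commonly leaves exact item wording to the full document. On this reading somatostatin simply stands for study treatment. This stands in part: it rules out asserting that control patients will not be asked. It does not remove the problem, because the printed items are introduced as the ones to be answered, item 6 shows that between-group wording was used where it was meant, and an infusion has no counterpart in the control arm as described.

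A second reply is that item 5 records the next rebleed in everyone, and its date would also show whether it fell within 8 days. This stands for delayed rebleeding. For 8-day rebleeding it is a partial remedy, since item 5 is headed late rebleeding and relies on monthly home visits.

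A third reply is that the safety sentence is an opinion in the Background, and that the primary variable is defined separately. Both are true. They limit the point to secondary outcomes; they do not make the wording fit the stated expectation.

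A reader might infer that no difference between the arms can be estimated at all. The document does not support that: items 5 and 6 apply to both arms, and the complete form is not shown.

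**Conclusion.** The point holds as a defect of printed wording. Four of the seven post-treatment items lack a defined time zero and an applicable question for control patients, while the Background expects better safety and less early rebleeding than with propranolol. Comparisons of the next rebleeding and of mortality remain possible. For tolerability, time to stopping of bleeding and 8-day rebleeding, missing or differently timed control data is a real risk, not an established fact.

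This rests on two assumptions: that the printed items reflect how the form will be worded, and that the control arm has no infusion, since none is described. If the full form already has neutral wording and a common clock, the remedy is only to correct the published list. No numerical size can be put on the bias from the document. The sample-size figures are unaffected.

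**What to change.** - Word items 1 to 4 as *after study treatment*.
- Date all four in both arms from one common time zero: randomisation, or the start of assigned treatment if that is defined for both arms.
- Use the same adverse-effect checklist and the same contact schedule in both arms.
- Compare the answers by allocated arm.
- Word item 7 as a between-group question where ultrasonography is done in both arms; if it is done in one arm only, present the result as a description of that arm.
- Base any safety statement on the adverse-effect comparison and not on rebleeding.

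The cost is slightly more form completion for control patients. Two reservations apply. Bringing item 7 to both arms adds no procedure only if control patients are already to be scanned. Equal contact schedules add no visits only if early contact is already planned for both arms. The document does not settle either.

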## Discussion

It is expected that the administration of somatostatin as a bolus followed by a 24 hour long infusion, will stop bleeding immediately, delay rebleeding as compared to the control study group and delay mortality in the somatostatin treated subjects. Our protocol that is based on a pilot study will help to establish the importance of somatostatin in schistosomiasis.
